## Abstract

**Background:**

Mindfulness meditation is a form of mind–body intervention that has increasing scientific support for its ability to reduce age-related declines in cognitive functioning, improve affective health, and strengthen the neural circuitry supporting improved cognitive and affective health. However, the majority of existent studies have been pilot investigations with small sample sizes, limited follow-up data, and a lack of attention to expectancy effects. Here, we present the study design of a Phase I/II, efficacy trial—HealthyAgers trial—that examines the benefits of a manualized mindfulness-based stress reduction program in improving attentional control and reducing mind-wandering in older adults.

**Methods:**

One hundred fifty older adults (ages 65–85 years) will be randomized into one of two groups: an eight-week mindfulness program or an eight-week, placebo-controlled, lifestyle education program. Behavioral and neuroimaging assessments are conducted before and after the training. Participants are then invited to booster sessions once every three months for a period of 12 months with post-intervention follow-up assessments conducted at 6-months and 12-months. The primary outcomes for the study are behavioral measures of attentional control and mind-wandering. Additional, secondary outcomes include network strength in an a priori defined neuromarker of attentional control, fluid and everyday cognition, emotion regulation strategy use, and markers of inflammation.

**Discussion:**

This study will establish the efficacy of a group-based, low-cost mind–body intervention for the inter-related facets of attentional control and mind-wandering in older adults. Strengths of this study include a well-designed, placebo-controlled comparison group, use of web/mobile application to track study adherence, and longitudinal follow-up.

**Trial registration:**

Clinicaltrials.gov (#NCT03626532). Registered August 4, 2018.

**Supplementary Information:**

The online version contains supplementary material available at 10.1186/s12877-022-03334-7.

## Background

Older adults are a rapidly growing sector of the U.S. population as adults over the age of 65 years are projected to almost double from 56 million in 2020 (17% of the population) to 95 million in 2060 (23% of the population) [1]. Maintaining cognitive faculties is an important public health goal as cognitive functioning is highly related to well-established markers of physical health, like systemic inflammation [2, 3], and plays a critical role in activities that help maintain independent living, like driving [4], and in emotion dysregulation [5–7]. Thus, cognitive functioning has direct implicatons for the well-being and satisfaction of older adults [8]. Age-related declines in cognitive functioning have been noted across the domains of processing speed, working memory, executive control of attention, cognitive control, and episodic memory [9–11], with declines in some domains of cognition beginning as early as the mid-30s [12]. Moreover, behavioral shifts in measures of cognitive functioning are also accompanied by concomitant shifts in the functional and structural integrity of the aging brain with older adults showing neural dedifferentiation—the reduced recruitment of specialized canonical networks and nodes during cognitive tasks with increasing age [13, 14]. These age-related declines in cognitive functioning, both behavioral and neural representations, are thought to be undergirded by the increase in task irrelevant observations with advancing age. Older adults demonstrate a failure to maintain attentional sets, to computationally prioritize task-relevant information, and to limit attentional overprocessing of task-irrelevant information, resulting in notable declines in higher-order control operations [15–17].

However, despite a more nuanced and in-depth understanding of the cognitive and neural changes associated with aging, the health field’s capacity to translate these findings into pragmatic, efficacious remediation methods remains limited. Cognitive training programs show modest improvements in overall cognition with limited benefits to tasks of everyday functioning [18, 19]. Although studies of strategy-specific cognitive training are able to identify factors that may mediate the impact of the intervention for changes in cognition, there have been limited far-reaching transfer effects [20, 21]. Comparatively, multi-modal interventions, combining across various training modalities [22, 23] show the most promising effects. However, in these studies, it has been difficult to isolate the mechanisms of action. Thus, the scientific premise of the current study is based on an urgent need to explore alternative training programs that provide theoretical promise for reducing age-related cognitive decline, particulary in attentional overprocessing of task-irrelevant information. This could then have broad transfer effects on emergent cognitive operations of cognitive control, emotion regulation, and for domains of cognitive functioning that directly impact everyday functioning, like driving.

Mindfulness training, traditionally offered as an eight-week program called the mindfulness-based stress reduction (MBSR) [24], has gained increased popularity for its potential to improve cognition [25, 26], ameliorate symptoms of depression and anxiety [27], alter perceived and objective markers of stress [28], enhance emotion regulation [29], and alter the neural circuitry supporting cognitive and emotional functioning [30, 31]. Mindfulness, as defined in the contemporary sciences, is the practice of purposefully directing attention, in a non-judgmental way, to observe the unfolding of each moment as it takes place [32]. As such, the various components of attention, including the fluctuations in attention—quantified via the propensity to engage in mind-wandering—are being investigated for their malleability as a function of engagement in mindfulness practices. In our recent scoping review of the contemplative sciences literature examining the impact of mindfulness meditation for components of attention, we found the most robust evidence for mindfulness training to impact executive control of attention [33]. Moreover, results of a pilot, randomized controlled trial in our lab also provided evidence for mindfulness training to reduce off-task thinking, or mind-wandering quantified using both self-reported thought probes and response time variability in healthy older adults [34]. These reductions in mind-wandering propensity, replicated by other clinical trials (see Feruglio [35] for a systematic review), provide preliminary support that training in mindfulness meditation may strengthen the goal maintenance system, enhancing one’s ability to prioritize task-relevant representations, and to filter out irrelevant, internal thoughts or external stimuili in the environment.

Taken together, there is a growing recognition for the potential for mindfulness practices to improve attentional control—the biasing of task-relevant representations at the temporal, spatial, and response stages. However, this literature is still in its infancy, particularly in the evidence supporting mindfulness meditation as a tool for reducing age-related cognitive decline. The majority of studies, including our own pilot clinical trial, have had limited follow-up data, have relied on self-reported data for quantifying adherence to study materials, and did not include broad measures of transfer effects. This Phase I/II efficacy trial—HealthyAgers—aims to build on the existing literature by examining the immediate and longitudinal impact, relative to an active control group, of an eight-week mindfulness-based stress reduction (MBSR) program in improving attentional control and reducing mind-wandering in older adults. In addition, the control group in the study—Lifestyle Education (LifeEd) program—has been carefully designed to match the training group for non-specific factors that may influence the outcomes of interest. Participants in both groups will engage in a booster session every three months across the 12-month period following the intervention. Importantly, we have designed an in-house web/mobile application—HealthyAgers—to measure engagement with study materials for both groups to allow for careful assessments of dose–response relationships. We hypothesize that mindfulness training, compared to lifestyle education training, will improve attentional control and reduce mind-wandering. Secondary measures of this study will also assess the broad impact of mindfulness meditation for functional connectivity, fluid and everyday cognition, emotion regulation, and systemic inflammation. We hypothesize that mindfulness training will additionally result in an improvement in these secondary measures of healthy aging. The results of this study will establish the efficacy of this increasingly popular, low-cost intervention for older adults with regard to cognitive, affective, and neural health.

## Methods/design

### Study design

The proposed study is a single-blind, randomized controlled trial (RCT) designed to examine the differential impact of mindfulness training compared to a lifestyle education group (LifeEd) on behavioral and neural measures of attentional control and mind-wandering. Secondary assessments involve measures of fluid cognition, everyday cognition, emotion regulation, and systemic markers of inflammation. One hundred fifty older adults (65–85 years old) are being recruited for the study and randomized to either an eight-week MBSR group or an eight-week LifeEd control group. Behavioral, neuroimaging, and inflammation data will be conducted at baseline prior to randomization and again at the conclusion of the eight-week intervention. Further, participants will be followed for an additional 12 months, during which time booster sessions will be provided once every three months, with cognitive and affective assessments performed at 6-month and 12-month follow-ups. Neuroimaging and inflammation data will only be collected at the 12-month follow-up. Figure 1 illustrates a timeline of study participation.

**Fig. 1 Fig1:**
[figure not shown]
Flowchart of the HealthyAgers Trial

### Setting

Assessments and the intervention will be conducted in the Psychology Building at The Ohio State University. The Department of Psychology houses individual neuropsychological testing rooms to allow for the convenient administration of neuropsychological and emotional regulation measures. All structural and functional MRI data will be collected at the Center for Cognitive and Behavioral Brain Imaging housed in the Department of Psychology at Ohio State. Prior to the onset of the COVID-19 pandemic, all intervention sessions were provided in the group therapy spaces housed in the Department of Psychology. These spaces were specifically designed for offering mindfulness and LifeEd sessions. Intervention sessions have been shifted to a virtual format following the COVID-19 pandemic, but assessment sessions continue to be collected in-person.

### Participant eligibility

Participants will only be included in the study if they satisfy the following criteria: aged between 65–85 years, corrected (far) visual acuity of 20/40 or better, have adequate hearing for assessment purposes, and have self-reported proficiency in spoken English and in reading comprehension. Additionally, we will only include participants if they are able to attend the majority of eight-week sessions and attend all assessment sessions, have a self-reported interest in engaging in mind–body interventions, can commit to a 30-min homework practice five times per week, and have the ability to engage in light stretching and toning exercises.

Additionally, participants will only be included in the study if they are classified as cognitively normal or having mild cognitive impairment (MCI) based on a battery of neuropsychological measures employed to screen individuals with dementia [36, 37]. The screening battery includes the following measures and seven dependent variables used for exclusionary determinations: 1) total recall and 2) delayed recall from the Hopkins Verbal Learning Test—Revised ([38], 3) total score on the Block Design and 4) total score on Digit Span subtests from the Wechsler Adult Intelligence Scale-IV [39], 5) total score on the FAS Verbal Fluency Task [40], 6) total score on the Boston Naming Test [41], and 7) perseverative errors on the computerized version of the Wisconsin Card Sort Test [42]. The WAIS-IV subtests are completed between the immediate and delayed recall tasks of the Hopkins Verbal Learning Test. Descriptions of each of these measures and details on their scoring and norms are provided in Supplementary Materials. Participants will be excluded from the study due to having impairment levels consistent with dementia based on one of the following criteria: 1) if at least one normed score in both the memory and non-memory domains is < -2 *S.D.*s below the mean (i.e., T < 30), 2) if the average of their normed scores on all seven neuropsychological measures is < -2 *S.D.s* (i.e., average T < 30), or 3) if the participant reports less than intact function on all items of the Lawton Instrumental Activities of Daily Living [43] (< 8/8 points).

Participants will be classified as having MCI if they do not meet the criteria for dementia but have at least one normed score < -1.5 *S.D.*s below the mean (i.e., T < 35) or if the average of their seven normed score is < -1.5 *S.D.*s (i.e., average T < 35). Participants will be classified as cognitively normal if all of their normed scores are within 1.5 *S.D.*s of the mean and they receive a full score on the Lawton Instrumental Activities of Daily Living. These categorizations are consistent with previous clinical definitions of MCI and dementia [44, 45] and with previous research in MCI and dementia classification [36, 37]. However, an important limitation with this approach is that, although our categorization of MCI may be consistent with clinical conceptualization, it has been demonstrated that a significant minority of healthy older adults will have at least one “impaired” score < -1.5 *S.D.*s from the mean when given a neuropsychological battery [46, 47]. This has been of particular concern when trying to characterize MCI [48, 49]. In the event that the normed scores for a participant are not able to be computed due to errors in a given test’s administration, the participant will be assessed for cognitive impairment using an electronic version of the Montreal Cognitive Assessment [50] with its provided cut-off scores (26/30 or higher denoting normal cognition).

Other reasons for exclusion of potential participants include if they have been previously diagnosed with a neurological disorder, an inflammatory disorder, or a terminal illness. Participants with a history of psychotic disorders, substance abuse, or a prior learning disability will also be excluded. Additionally, participants diagnosed with a psychiatric disorder in the last two years by a mental health professional and those scoring greater than 19 on the Center for Epidemiologic Studies Depression Scale [51] will be excluded from the study. Participants currently taking medications belonging to any of the following drug classes will be excluded: sedatives, selective serotonin reuptake inhibitors, benzodiazepines, barbiturates, sedative-hypnotics, anti-inflammatories, chemotherapies, and any drugs altering brain function or enhancing cognitive performance. Anyone who has engaged in formal mindfulness training within the past year will also be ineligible or with current regular practice of meditation—defined as practicing any kind of meditation practice for greater than 10 min per day—will be ineligible. As the study involves participants engaging with practices on a web/mobile platform, participants will also be excluded from the study if they do not have access to the internet. Participants without access to computers but with internet access will be provided mini-iPads.

### Sample size

In our pilot study [34], we found a partial eta square of 0.088 for the repeated-measures ANOVA examining the effect of mindfulness on Go/No-Go performance as a function of working memory index. Based on an alpha of 0.05, a total sample size of 103 would be needed to yield an estimated power greater than 0.80. Given the attrition observed in our pilot study (~ 20%), the 12-month duration of the proposed intervention, and multiple assessment sessions, we will recruit at least 130 participants to account for a potential 25% drop-out rate. Power analysis for the imaging data was based on the parameter estimates in the Kilpatrick study [52] examining the impact of mindfulness training on functional connectivity of resting-state networks. The resulting effect sizes were *d* = 1.29 and *d* = 0.99 for auditory/salience regions To be conservative, we used the effect size of *d* = 0.99. To detect an effect of this size with 90% power, we would need 23 subjects per group for a total of 46 people. A study by Kilpatrick and colleagues [52] compared their mindfulness intervention against a wait-list control group. It is likely that the parameter estimates of their study include variance that may be accounted for by non-specific factors. In the present study, our mindfulness training group will be compared with an active control group that will control for many of the non-specific factors. Thus, assuming an effect size of *d* = 0.76, we plan on collecting MRI data on 75 participants to yield an estimated power greater than 0.90.

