### Randomization

Eligible and consenting participants will be randomized after completing baseline assessments to one of two groups: MBSR or LifeEd. A random permuted-block design (blocks of size 2 and 4) will be used, and the randomization with an allocation ration of 1:1 will be stratified by sex assigned at birth (male, female), cognitive status (cognitively normal, MCI), and MRI eligibility (eligible, not eligible) to ensure balance across these important factors. The biostatistician on the team, [name], prepared and maintains the randomization sequence for the eight strata. The project coordinator has been given concealed envelopes and only after a participant completes all pre-assessment sessions and is deemed eligible for the study does the project coordinator open the envelope from the respective stratum and assign the participant to either the MBSR or the LifeEd group. The project coordinator, the study facilitators and supervisors, and the study biostatistician will be the only members of the team who will be unblinded to group assignment. All personnel conducting assessments, behavioral or neuroimaging, will remain blind to group assignment.

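### The recruitment floor of 130 does not cover the stated 25% drop-out: it leaves 97 of the 103 participants required, and 138 would be needed

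*Protocol article*

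**What the plan says.** All the sample-size reasoning for the behavioural outcomes is in the Sample size section of the protocol article. It starts from the pilot trial: "we found a partial eta square of 0.088 for the repeated-measures ANOVA", for an effect described as depending on working memory index. "Based on an alpha of 0.05", it states that "a total sample size of 103 would be needed to yield an estimated power greater than 0.80". It then cites pilot attrition of about 20%, the 12-month duration and the repeated assessments as reasons to plan for greater loss, and concludes: "we will recruit at least 130 participants to account for a potential 25% drop-out rate".

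The trial size appears in two other places. The Methods paragraph of the abstract gives 150 older adults who "will be randomized into one of two groups: an eight-week mindfulness program" or the control programme. The Study design section likewise opens its enrolment statement with "One hundred fifty older adults". The Sample size section does not mention 150, and nothing elsewhere links 150 to the power calculation or to a drop-out allowance.

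**The concern.** A drop-out allowance should return the required number of participants once the assumed loss is taken off. Here it does not. The floor is offered as sufficient for 25% loss, yet removing 25% leaves fewer than the 103 that the same paragraph requires. The enrolment figure that would be sufficient, 150, is given without a justification.

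What is at stake is the soundness of the printed justification. The floor of 130 is the only recruitment number that the document argues for. Recruitment was still under way when the article was written, and a trial that closed at 130 would satisfy the Sample size section while missing its requirement under its own drop-out assumption.

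**Working it through.** **Inputs, all from the Sample size section unless noted.** Partial eta squared 0.088; alpha 0.05; required total 103 for power above 0.80; pilot attrition about 20%; planned drop-out 25%; recruitment floor 130. Enrolment of 150 is from the abstract and Study design. Allocation is 1:1 (Randomization).

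**Step 1: reproduce 103.** Effect size f² = 0.088/(1 − 0.088) = 0.0965, so f = 0.311. Power is taken from the non-central F distribution with non-centrality N × f², u numerator df and N − u − 1 denominator df. The document does not state u, so it is an assumption here. The smallest N with power of at least 0.80 is:

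- u = 1: N = 84
- u = 2: N = 103 (power 0.8004)
- u = 3: N = 117

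Of these, only u = 2 returns the protocol's figure.

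**Step 2: check the drop-out allowance.** This step uses only printed figures and no power model.

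- Remaining from 130 after 25% loss: 130 × (1 − 0.25) = 97.5, so 97. That is 103 − 97 = 6 short.
- Largest loss that 130 can absorb: 1 − 103/130 = 0.208, or 20.8%.
- Number needed to keep 103 after 25% loss: 103/(1 − 0.25) = 137.3, so 138. The floor is 138 − 130 = 8 too low.

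**Step 3: check 150.**

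- Remaining after 25% loss: 150 × 0.75 = 112.5, so 112, which exceeds 103.
- Largest loss that 150 can absorb: 1 − 103/150 = 0.313, or 31.3%.

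**Step 4: power at the resulting numbers, over the range of unstated df.**

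| Numerator df (assumed) | N = 97 (130 less 25%) | N = 103 (required) | N = 112 (150 less 25%) |
|---|---|---|---|
| 1 | 0.857 | 0.878 | 0.903 |
| 2 | 0.774 | 0.800 | 0.835 |
| 3 | 0.710 | 0.740 | 0.780 |

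On the 2 df row, which matches the protocol's 103, moving from 103 to 97 costs 0.800 − 0.774 = 0.026, about 2.6 percentage points.

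**Step 5: where 130 might come from.** Two routes give the same 128.75: 103 × 1.25 (multiplying up by the drop-out rate) and 103/0.80 (correct division, but at the pilot's 20%). Either would round up to 130, so the arithmetic cannot separate them.

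**The case against.** The case for leaving the text alone has several parts, and some of them stand.

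*The two enrolment figures agree.* A reader might infer that 130 and 150 contradict each other. They do not. The Sample size section sets a minimum, and 150 satisfies it. What remains is that the section does not connect its minimum to the stated enrolment.

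*The trial is adequately sized.* A reader might infer that the trial is underpowered. The document does not support that: 150 less 25% leaves 112, above 103, and no section plans to stop at 130.

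*Power below 0.80 at 97 is not established.* This stands. The value 0.77 depends on 2 numerator df, inferred only because it returns 103. The immediate-effect test in Data management and analysis (two groups, two timepoints) has 1 df for the interaction, and on 1 df 97 participants give 0.857. The pilot effect involved working memory index, so its df cannot be recovered from the document. What can be said is that 97 is below the protocol's own requirement.

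*The loss may matter less than it looks.* The 25% is tied partly to the 12-month duration, whereas the immediate effect is tested after eight weeks. At the pilot's 20% loss, 130 × 0.80 = 104, which suffices. The planned mixed models can use partial follow-up, and the protocol intends to assess people who stop the intervention. All this softens the consequence. It does not repair the sentence, which names 25% and takes no credit for partial data.

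*The cause is unknown.* It is tempting to call this the familiar slip of multiplying by 1.25 instead of dividing by 0.75. Because division at the pilot's 20% gives the same number, that remains conjecture.

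**Conclusion.** The concern holds in a narrow form. The statement that 130 accounts for 25% drop-out from 103 is arithmetically wrong on the document's own figures, by 8 recruited participants or 6 completers. This conclusion rests on no modelling assumption. The accompanying loss of power is uncertain: about 2.6 points if the calculation used 2 df, and undetermined otherwise.

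The severity is minor. Enrolment at 150 already exceeds what 25% loss requires, so design, analysis and enrolment are unaffected at the stated size. The defect is an incorrect justification that stands apart from the enrolment figure able to support it.

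**What to change.** Amend the one sentence in the Sample size section, in either of two ways:

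- replace the floor of 130 with at least 138, showing 103/0.75; or
- make the stated 150 the basis, say that about 112 remain after 25% drop-out, and restate the power for that number with its numerator df given. On the 2 df calculation that reproduces 103, the power is about 0.84.

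The second is preferable, because it ties the justification to the enrolment already declared and removes the need for a separate floor. In either case, use one recruitment figure in the abstract, Study design and Sample size. The cost is one sentence, with no participants beyond the 150 already stated.

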#### Neuroimaging assessment

Functional MRI (fMRI) and structural MRI data will be collected at pre-training, post-training, and at 12-month follow-up. The primary dependent variable from the neuroimaging data is the network strength in a connectome-based predictive model of sustained attention (saCPM; [62]). Figure 2 presents the functional neuroanatomy of the high attention model (includes functional connections that positively predict attentional control) and the low attention model (includes functional connections that negatively predict attentional control). The saCPM model, combining the functional connections of the high and low attention models, will be employed in the current study. Network strength in this whole-brain, functional connectivity-based model of attentional control predicts performance on variegated tasks of attentional control [63–65], generalizes to predict performance across young adults [66], older adults [65], and individuals with attention-deficit hyperactivity disorder [62], and, critically, shows responsiveness to change following methylphenidate treatment for attention-deficit hyperactivity disorder [63]. Participants will perform the gradual-onset continuous performance task (gradCPT; [62, 67, 68]) while in the scanner. In this task, participants view circular images of city and mountain scenes. Participants are asked to respond to the frequently occurring city scenes (~ 90% of images) and to withhold responses to mountain scenes. Participants will complete two separate runs with each run lasting 13 min and 44 s. Neuroimaging data will be checked for quality control and preprocessed using our lab’s established pipelines [69]. The preprocessed 4D data for each participant will be parcellated into 268 contiguous and functionally defined regions using a parcellation scheme covering the cortex, subcortex, and cerebellum [70]. The connections between each pair of these nodes, defined as edges, will be computed by correlating the time-course of activity between the nodes. This will result in a 268X268 functional connectivity matrix with cells of the matrix representing the magnitude of these edges or correlations. Using the network mask of the saCPM neuromarker [63], which has been validated in our prior work with older adults [71], we will compute the network strength of the marker for each participant at pre-training, post-training, and at 12-month follow-up.

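### The imaging power of more than 0.90 holds only if all 75 MRI participants are analysed; if 75 is the number scanned at baseline, the plan's own 25% loss leaves about 0.80

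*Protocol article*

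**What the plan says.** The Sample size section of the protocol article makes two calculations.

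- **Behavioural.** It finds that 103 participants are needed at alpha 0.05 for power above 0.80. It then cites pilot attrition of about 20%, the 12-month duration and the repeated assessments, and concludes "we will recruit at least 130 participants to account for a potential 25% drop-out rate".
- **Imaging.** It starts from d = 0.99 in a cited wait-list-controlled study, for which at 90% power "we would need 23 subjects per group for a total of 46 people". Because this trial has an active control, it lowers the effect, "assuming an effect size of *d* = 0.76", and concludes "we plan on collecting MRI data on 75 participants to yield an estimated power greater than 0.90". No drop-out allowance follows.

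Under Neuroimaging assessment, functional and "structural MRI data will be collected at pre-training, post-training, and at 12-month follow-up". That section names network strength in the sustained-attention model as the main imaging variable and says that scans will be checked for quality. The section heading Secondary outcomes places imaging among the secondary measures. Data management and analysis says that the secondary measures will be examined with linear mixed models.

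**The concern.** One paragraph treats loss in two ways: the behavioural sample is enlarged for it and the imaging sample is not. The reasons given for the behavioural allowance (pilot attrition, length of follow-up, repeated visits) apply equally to the people who are scanned, since they are trial participants who must return for scans after training and at 12 months. A participant with only a baseline scan adds little to the estimate of a Group by Time effect, so power depends on how many have usable repeat scans.

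At stake is how a null result on network strength would be read. A reader told that power exceeded 0.90 takes the chance of missing the assumed effect to be under 10%. If 75 are scanned at baseline and a quarter are lost, that chance is about 20%.

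**Working it through.** **Inputs.** From Sample size: d = 0.76; MRI data on 75 participants; planned drop-out 25%; pilot attrition about 20%. From Randomization: 1:1 allocation, stratified by MRI eligibility. Alpha 0.05 is stated for the behavioural calculation only. Two-sided 0.05 is my assumption for imaging, tested in step 1.

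**Formula.** Two-sample t-test with group sizes n1 and n2: df = n1 + n2 − 2; non-centrality δ = d × √(n1·n2/(n1 + n2)); power = P(|T| > t at 0.975 with df), where T is non-central t with df and δ.

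**Step 1: check the assumed method on the plan's other imaging figure.** With d = 0.99 and 23 per group, δ = 0.99 × √11.5 = 3.357 and power is 0.907. With 22 per group it is 0.894. So 23 per group is the smallest size reaching 90%, as the plan says. One-sided 0.05 would give 0.952 at 23 per group, so 23 would be larger than needed. Two-sided 0.05 fits.

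**Step 2: reproduce the stated power.** With 38 + 37 = 75 analysed, δ = 0.76 × √(38 × 37/75) = 3.291, df = 73, critical value 1.993, power **0.901**. With 37 + 37 = 74, δ = 3.269 and power is **0.897**. The stated figure is reproduced, and 75 is the smallest total that exceeds 0.90.

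**Step 3: apply loss, if 75 is the number scanned at baseline.**

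| Loss | Source of rate | Analysed | Power at d = 0.76 |
|---|---|---|---|
| 0% | implied by the plan's figure | 75 | 0.901 |
| 10% | my assumption for 8 weeks | 75 × 0.90 = 67.5 | 0.868 |
| 20% | pilot attrition | 75 × 0.80 = 60 | 0.825 |
| 25% | plan's drop-out rate | 75 × 0.75 = 56.25, taken as 28 + 28 | 0.798 |

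For the last row, δ = 0.76 × √14 = 2.844, df = 54, critical value 2.005. Without rounding to whole participants (56.25), power is 0.799.

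**Step 4: detectable effect.** Solving the same formula for 90% power gives d = 0.759 with 75 analysed and d = 0.882 with 56 analysed.

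**Step 5: baseline scans needed for 75 completers.** 75/(1 − 0.25) = 100.

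**Sensitivity to sidedness.** With one-sided 0.05 and 25% loss, power is about 0.88, still below 0.90.

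**The case against.** The strongest reply is that nothing is miscalculated and that 75 may already be a completer count. The first part is correct: for 75 analysed participants the stated power is right. The second part is possible. The text never says that 75 is the baseline number. The Abstract and Study design give a total of 150, Table 2 schedules imaging without a sub-sample limit, and its footnote excuses only those with MR contraindications. About 100 baseline scans would be 100/150 = 67% of 150, or 100/130 = 77% of 130, and the design might supply that. The protocol gives no MRI eligibility rate, so the question stays open. A reader might infer that the design fails to deliver 90% power; the document does not support that as a flat statement. What stands is that the paragraph allows for loss in one sample and is silent on it for the other.

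A second reply is that 25% is justified by the 12-month duration, while the immediate-effect model uses only pre- and post-training data. That also stands. Loss at 8 weeks may be smaller, so the 0.80 figure belongs mainly to the 12-month comparison. But 75 has no margin, so any loss at post-training still takes power below 0.90.

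A reader might also infer that 0.76 was chosen to fit 75 scans, since 0.759 is the detectable effect at that size. The protocol does argue for a downward adjustment from 0.99, and although it does not derive the exact value, a numerical match does not show how it was chosen. Losses from scan quality checks are likewise plausible, but the document gives no rate, so none is included above.

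**Conclusion.** The point holds in conditional form. Power above 0.90 at d = 0.76 is correct for 75 analysed participants and for no fewer. The protocol does not say that 75 is the analysed number, and it applies its drop-out allowance only to the behavioural sample. If 75 is the baseline number, power falls to between about 0.87 (10% loss) and about 0.80 (25% loss).

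This rests on two-sided 0.05, a two-sample t approximation to the mixed-model contrast, loss spread evenly over the groups, and little information from participants with a baseline scan only.

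The weight is moderate. Network strength is secondary, the primary sample size is untouched, and even at 25% loss the power is close to the 0.80 that the trial plans for its behavioural outcome. The consequence is a power claim that may be too favourable, which matters chiefly if the imaging result is null.

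**What to change.** State whether 75 is the number scanned at baseline or the number with usable repeat scans, and replace the power sentence with one that is true in both cases, for example:

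*With 75 analysed participants power is 0.90 for d = 0.76; if 75 are scanned at baseline and 25% are lost (about 56 analysed), power is about 0.80 and the effect detectable with 90% power is d = 0.88.*

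If 75 is a completer target, add that 25% loss implies about 100 baseline scans. The new wording should not assert that 75 is the baseline count unless the sponsor confirms it.

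The cost is one or two sentences and, if 75 is the baseline number, a less favourable power figure. Restating the figure needs no extra scans.
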